## Abstract

**Background:**

Stroke affects many aspects of life in stroke survivors and their family, and returning home after hospital discharge is a key step for the patient and his or her relatives. Patients and caregivers report a significant need for advice and information during this transition period. Our hypothesis is that, through a comprehensive, individualised and flexible support for patients and their caregivers, a patient-centred post-stroke hospital/home transition programme, combining an Internet information platform and telephone follow-up by a case manager, could improve patients’ level of participation and quality of life.

**Methods:**

An open parallel-group randomized trial will be conducted in two centres in France. We will recruit 170 adult patients who have had a first confirmed stroke, and were directly discharged home from the stroke unit with a modified Rankin score ≤3. Intervention content will be defined using a user-centred approach involving patients, caregivers, health-care professionals and social workers. Patients randomized to the intervention group will receive telephonic support by a trained case manager and access to an interactive Internet information platform during the 12 months following their return home. Patients randomized to the control group will receive usual care. The primary outcome is patient participation, measured by the “participation” dimension score of the Stroke Impact Scale 6 months after discharge. Secondary outcomes will include, for patients, quality of life, activation, care consumption, as well as physical, mental and social outcomes; and for caregivers, quality of life and burden. Patients will be contacted within one week after discharge, at 6 and 12 months for the outcomes collection. A process evaluation alongside the study is planned.

**Discussion:**

Our patient-centred programme will empower patients and their carers, through individualised and progressive follow-up, to find their way around the range of available healthcare and social services, to better understand them and to use them more effectively.

The action of a centralised case manager by telephone and the online platform will make it possible to disseminate this intervention to a large number of patients, over a wide area and even in cases of geographical isolation.

**Trial registration:** ClinicalTrials NCT03956160, Posted: May-2019 and Update: September-2021.

**Supplementary Information:**

The online version contains supplementary material available at 10.1186/s12913-022-07907-5.

## Background

With the improvement of acute care organisation, stroke prognosis is continually improving [1], and the number of patients returning home directly after acute stroke unit management is dramatically increasing [2]. For instance, in France, 70% of patients return home directly after treatment in a stroke centre [3], and this is a key step for the patient and his or her relatives [4]. Due to the brutality of stroke and increasingly shorter lengths of hospital stay, patients and their families experience great difficulties adapting quickly to the patient's new state of health or dependence and the new caregiver role of family members. Following the acute phase treatment, the patient’s care pathway involves several different types of health and social workers. However, the healthcare system is complex and difficult for patients and their caregivers to understand [5], and there is a lack of support and of relevant, scientifically validated, information during the transition from hospital to home; this has significant negative consequences for the patient (reduced functional prognosis, quality of life, increased risk of recurrence) and his or her caregiver (increased perceived burden, decreased quality of life, socio-economic impact) [5, 6]. Patients and caregivers report a significant need for advice and information during this transition period. They seek individualised, good quality information that changes in nature over time in line with the evolution of the needs and recovery of the patient [7, 8]; the provision of information through an Internet platform could meet these characteristics, in association with tailored support by a case manager to ensure continuity of care and improve care pathway. Existing transition programmes mainly focus on home functional rehabilitation and do not offer a comprehensive approach, responding to patients and caregivers needs that are wider [9–13]. The recently published MISTT trial conducted in the United States showed that such a programme, associating a social worker-led case management and a dedicated website, had promising results providing a significant improvement in patient-reported outcomes related to physical health [14, 15]. However, the authors acknowledged that the mechanisms of actions of the intervention remain uncertain since the website use by patients was limited and no process evaluation alongside the trial had been conducted [16]. In addition, the transferability of the programme had not been studied and sociocultural differences might hinder the generalisation of conclusions to other healthcare contexts. In France, no such program has been developed to date for stroke, this is why we aim to develop a stroke transition program in partnership with patients and families, and assess its efficacy. Our hypothesis is that, through a comprehensive, individualized and flexible support for patients and their caregivers, a patient-centered post-stroke hospital/home transition program, combining an Internet information platform and telephone follow-up by a case manager, could improve patients’ level of participation and quality of life. We present herein the protocol for the NAVISTROKE trial, a superiority randomized controlled trial evaluating the efficacy of this programme.

## Objectives

The main objective of the trial is to assess the impact of a patient-centred post-stroke transition programme, combining an Internet information platform and telephone follow-up by a case manager, on changes in the level of patient participation, evaluated by the Stroke Impact Scale (SIS), 6 months after their return home compared to usual care. The transition programme aims to empower patients and their caregivers, and help them to identify, understand and use the available medical and medico-social services according to their needs to improve their recovery. Secondary objectives are to study the efficacy of the programme on the following patient-reported outcomes: patients’ level of activation, quality of life, anxiety, depression, fatigue, and sleep quality at 6 and 12 months; on patients’ functional prognosis, attainment of targeted cardiovascular risk factor objectives, healthcare access, as well as occupational and social functioning at 12 months. We will also measure the efficacy of the programme on informal caregivers’ burden, quality of life, anxiety, depression, and occupational and social functioning. A process evaluation of the intervention implementation will be conducted using a mixed-method approach based on the Medical Research Council guidance [17, 18]. Semi-structured interviews will be conducted to understand the barriers and facilitators perceived by patients and the case manager.

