#### Secondary outcomes

Participation at 12 months: participation score at 12 months after discharged home (SIS). Quality of life at 6 and 12 months: scores of the other dimensions of the SIS at 6 and 12 months: force dimension, manual function, activities of daily living/instrumental activities of daily living (ADL/IADL), mobility, communication, emotions, memory/thinking, as well as global recovery.

Anxiety and depression scores: change of anxiety and depression scores between discharge home and 6 months, and discharge home and 12 months, measured by the Hospital Anxiety and Depression Scale (HADS) score [31]. Fatigue, sleep quality, and sleepiness: changes in fatigue level measured by the Pichot scale [32], sleep quality measured by the Pittsburgh scale, and sleepiness level measured by the Epworth scale between discharge home and 6 months, and discharge home and 12 months. Epworth scale licence will be obtained before the first inclusion.

Prognosis at 12 months after discharge home: stroke recurrence within 12 months, reported by the patient and/or caregiver and validated by checking the hospital discharge report; unscheduled hospitalisations or emergency room visits within 12 months of discharge from hospital to home reported by the patient and/or caregiver and validated by checking the hospital discharge report; m-RS at 12 months; death at 12 months reported by the caregiver; cognitive disorders at discharge to home and at 12 months, measured by the Montreal Cognitive Assessment (MOCA) scale [33, 34].

Prevention of cardiovascular risk factors: last known blood pressure, LDLc, and glycaemia values, as well as smoking status, physical activity, and body mass index at baseline, 6, and 12 months; these data will be collected by interviewing the patient or in the electronic medical record.

Access to care and social services at 12 months: consumption of care (consultations and hospitalisations) and perceived social aids; these data will be collected by interviewing the patient.

Maintain of the hospital discharge prescriptions at 6 and 12 months (persistence): 6 and 12 months maintenance of secondary treatments for stroke prescribed at discharge, and reasons for discontinuation if applicable; these data will be collected by interviewing the patient and a copy of medical prescriptions will be collected.

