### Sample size

The study will be powered to detect a difference of 15 points in the SIS-Participation score at 6 months of follow-up between the TAU and the intervention group. A 15-point difference between groups in SIS-P score is considered clinically relevant [40]. To detect this difference, 70 patients per group is needed (assuming a common SD of 27 according previous results from the STROKE-69 cohort, power=90%, bilateral alpha level=0.05). Accounting for 20% attrition, we plan to recruit a total of 170 patients.

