### Statistical analysis

Categorical variables will be presented using numbers and percentages, and quantitative variables using mean and standard deviation or median and interquartile range according to their distribution.

Group difference in the SIS Participation domain score at 6 months after hospital discharge will be analysed using a linear model adjusted on the stratification factors (centre and presence or caregiver). The primary analysis will be performed in accordance with the intention-to-treat principle (an imputation method for missing data will be used when appropriate). In a modified intention-to-treat analysis and per-protocol analysis, patients who died before 6 months or those with stroke recurrence before 6 months will be excluded. Change in the SIS participation domain score between 6 and 12 month after discharge will be compared between groups using linear mixed effects model. The model will include patients as random effect, time (6 and 12 months), group (TAU or intervention) and an interaction effect of treatment group × time as fixed effects after controlling for the stratification factors.

Continuous secondary outcomes will be assessed in a similar way. Categorical data will be analysed using logistic or survival models. For non-repeated continuous and binary measurements, ordinary linear regression and logistic or Cox proportional-hazards models will be used when appropriate.

A detailed statistical analysis plan will be made prior to database lock. Analysis and reporting of the results will follow the CONSORT guidelines for reporting randomised controlled trials [45]. Analyses will be conducted using SAS software (version 9.4; SAS Institute Inc., Cary, NC, US). All tests will be two-sided and carried out at the 5% level of significance.

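### The secondary objective names attainment of cardiovascular risk-factor targets at 12 months, while the outcome section lists only the underlying values and statuses, and the analysis section does not say which form is analysed

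*Protocol article*

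**What the plan says.** In the protocol article, the Objectives section includes "attainment of targeted cardiovascular risk factor objectives" in a list of secondary objectives set at 12 months. The quantity named there is whether targets are reached.

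Under Secondary outcomes, the corresponding item is headed "Prevention of cardiovascular risk factors". It lists "last known blood pressure, LDLc, and glycaemia values, as well as smoking status, physical activity, and body mass index at baseline, 6, and 12 months", and adds that "these data will be collected by interviewing the patient or in the electronic medical record". It contains no at-target variable and no proportion attaining targets.

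The Statistical analysis section then gives general rules: "Continuous secondary outcomes will be assessed in a similar way. Categorical data will be analysed using logistic or survival models". The continuous models it describes are adjusted for the stratification factors (centre and caregiver). The mixed model has 6 and 12 months as its time points. No baseline covariate is named. A detailed analysis plan is promised before database lock.

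**The concern.** Attainment and measured value are different endpoints, even when both come from the same reading. A patient already at target whose LDLc falls further changes the group mean but not the attainment rate. A patient just above target who drops just below it changes the attainment rate but hardly moves the mean. A comparison of values therefore does not directly answer an objective about reaching targets.

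Two things are at stake. First, a reader of the final report could not tell from this article which comparison was the planned one. Second, the trial is open, data are entered as they are collected, and the article requires the analysis plan only before database lock. As written, nothing stops the form of this endpoint and its cut-offs from being settled once 6- and 12-month values are on file. Attainment adds a further open choice: each factor separately, a count of factors at target, or all targets together.

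**Working it through.** The plan gives no figure for this outcome, so the check is a comparison of the sections.

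| Section of the protocol article | What it names for cardiovascular risk factors | Time |
|---|---|---|
| Objectives | Attainment of targets | 12 months |
| Secondary outcomes | Last known blood pressure, LDLc and glycaemia; smoking status; physical activity; body mass index | Baseline, 6 and 12 months |
| Table 2 (study schedule) | No row for these measures | Not applicable |
| Statistical analysis | Continuous outcomes handled like the primary; categorical outcomes by logistic or survival models | Not specific to this outcome |

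1. **Time.** Twelve months is one of the three collection times, so the objective and the outcome agree on when.

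2. **Quantity.** The objective names a status against a target. The outcome item names readings and statuses. Blood pressure, LDLc, glycaemia and body mass index are continuous; smoking is a status; the form of physical activity is not given. Attainment can be derived from these data, but the item does not say that it will be. Elsewhere the article does define a derived yes/no outcome when it wants one: return to work is set at one day per week or more, equal to 10% of full-time employment.

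3. **Model.** The analysis rules depend on variable type. Attainment as yes/no would go to a logistic model, and blood pressure as a value to a linear or mixed model. The rules fit either form and select neither. Table 2 does not help.

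4. **Baseline adjustment.** The text "Continuous secondary outcomes will be assessed in a similar way" carries over models whose fixed effects are group, time (6 and 12 months), their interaction and the stratification factors. The risk factors are also recorded at baseline, but that value enters no stated model. If a baseline value correlates r with its 12-month value within groups, adjusting for it multiplies the residual variance by about 1 − r². The documents do not give r, so the gain cannot be quantified here. It uses data already collected and costs one degree of freedom.

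5. **Bearing on the main result.** The only sample-size calculation concerns participation: "The study will be powered to detect a difference of 15 points in the SIS-Participation score at 6 months of follow-up". With SD 27, two-sided 5% and 90% power, n per group = 2 × (1.960 + 1.282)² × 27² / 15² = 68.1, so 69. The t-test version gives 69.06, rounded up to the plan's 70. No term in it involves cardiovascular risk factors.

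**The case against.** The strongest reply is that an objective states an aim and an outcome list states what is recorded. All the inputs for attainment are listed, 12 months is among the times, and a condensed article may leave derivation rules and cut-offs to the full protocol or analysis plan. Most of this stands. Missing numeric targets are not a finding, and it would be wrong to say that the objective cannot be answered from the data. What remains is narrower: two sections of one document name different quantities for the same objective, and the third does not choose between them.

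A reader might infer a contradiction in timing. There is none.

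A reader might also infer that the plan has committed itself to a yes/no variable per patient in one place and a comparison of means in the other. Neither is stated. Attainment could be scored per factor or as a count, and the outcome item lists data without naming a comparison.

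Finally, a reader might see a large loss of power. With 170 × 0.8 / 2 = 68 patients per arm, normal values and an assumed shift of 0.4 SD, comparing values has 64% power. Comparing attainment has 46%, 39% or 33% when control attainment is 50%, 70% or 80%. At 0.2 SD the figures are 21% against 12% to 15%, and neither form is informative. These shifts and control rates are assumptions, since the article gives no cardiovascular effect size. The figures show only the general cost of dichotomising a continuous variable. They neither demonstrate the inconsistency nor show that the attainment objective should be dropped.

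**Conclusion.** The point holds as a minor inconsistency in one secondary outcome. The objective is attainment of targets, the outcome item lists values and statuses, and the analysis section leaves the form open. It does not affect the primary analysis or the sample size. No numerical size can be attached from the documents, because they give neither an expected effect nor a variance for these measures. The conclusion rests on the article's text alone. If the full protocol or the analysis plan already defines attainment and fixes the targets before follow-up values are examined, only the wording of the article needs aligning. The missing baseline covariate is a small, separate improvement: the plan as stated is valid without it but forgoes precision.

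**What to change.** Make the Objectives and Secondary outcomes sections name the same endpoint, by one of two routes:

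- Keep the objective. Add to the cardiovascular item an attainment outcome at 12 months, derived from the listed data, stating whether it is per factor or combined. The clinical team should fix the targets before any follow-up value is examined; which targets apply is theirs to decide.
- Alternatively, align the objective with the measures collected. All six should be carried over, including smoking status and physical activity.

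With either route, state that blood pressure, LDLc, glycaemia and body mass index are analysed as continuous values, with the baseline value as a covariate in addition to centre and caregiver, and that smoking status is analysed as a categorical outcome. Say what form physical activity takes, and add a row for these measures to Table 2.

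The cost is a few lines of text and an early decision on targets if the first route is taken. No new data, visits or patients are needed. The second route does change the stated aim from reaching targets to the measures themselves, so that choice belongs to the trial team.

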## Methods/design

The reporting of the study protocol follows the SPIRIT guidelines [19], the description of the planned intervention is guided by the template for intervention description and replication (TIDieR) checklist [20]. Patient and public involvement is reported according to the GRIPP2 reporting checklist [21].

### Study design

The NAVISTROKE trial is a 2-phase study; the first phase will consist in developing the intervention using a user-centred design approach, and the second phase is an open multicentre parallel-group superiority randomized trial. The study will be conducted in two stroke units in France. For qualitative study, semi-structured interviews will be conducted with patients, caregivers and the case manager: between fifteen and twenty interviews will be planned depending on data saturation. This number is planned based on available literature on data saturation [22, 23], however, if new information emerges from the final interviews, additional interviews will be planned.

### Setting and patients

The target population is composed of adult acute stroke patients managed in the participating stroke units. In the Rhône county (1,859,524 inhabitants), two stroke units manage acute stroke patients: one stroke centre in the Lyon University neurological hospital, including 12 acute stroke beds, and one stroke unit in a general hospital in the north of department with 6 acute stroke beds. Stroke neurologists will recruit adult patients who have had a first confirmed ischemic or haemorrhagic stroke managed in the participating stroke units, living in the Rhône department, and whose discharge from the stroke unit directly home is planned. The study will include only patients presenting a modified Rankin score (m-RS) of 1 to 3 at discharge from the stroke unit. Patients presenting with aphasia may be included if an informal caregiver is willing to commit to participate in the follow-up with the case manager. Neurologists should inform patients and their caregivers and obtain their consent before their inclusion in the study. Patients already living in an institution prior to stroke, or unable to communicate in the case of absence of informal caregiver or unwillingness to participate in the follow-up will not be included.

### Randomization

Before discharge from hospital, patients will be randomly assigned to one of the 2 groups at a 1:1 ratio. Randomization will be stratified on centre and presence of a caregiver, and will be centrally allocated using the Ennov Clinical® software (version 8.2.0). Allocation sequence will generate by statistician.

Figure 1 presents the study flowchart.

### Intervention

Patients in the intervention group will receive telephone support by a trained case manager (number and frequency of contacts defined according to the patient’s needs) and access to an Internet information platform for a 12-month period after returning home following hospital discharge. The planned intervention is described in Table 1. It aims to improve patients’ ability to manage their situation and meet their needs upon returning home, including identifying and requesting the necessary health or social resources. The detailed intervention content will be codesigned during the first phase of the study, using a “user-centred design” approach [24] including the following steps: identification of end-user needs, prototyping/development of the intervention (case management procedures and platform), iterative improvement, end-users testing (Fig. 2). Four workshops involving end-users of the intervention will be planned. This will ensure that the intervention aligns with the context and integrates both experience from professionals’ skills and practices on the one hand, and patients’ and caregivers’ experiential knowledge on the other hand. The intervention content will be underpinned by the cognitive social theory [25, 26] and based on scientific literature, an overview of existing local organisations and the results from previous studies our team conducted on patient needs following the acute phase [27, 28]. The logic model of the intervention (case management + Internet information platform) making the link with the theory and expected outcomes is presented in Fig. 3. For the user-centred design approach, an advisory committee, composed of patients and caregivers, health professionals, social workers, and public health and social sciences researchers, will be formed. This committee will meet during 4 participatory co-design workshops facilitated by a social science researcher and will all last 2.5-3 hours. Following the grid described in Table 1, the advisory committee will: define the case manager’s profile, and required knowledge and skills; identify the resources and tools to be proposed on the Internet information platform; test the tools and content; refine the programme evaluation criteria; and test and validate the study procedures.

**Table 1 Tab1:** Agenda of the co-design workshops during the user-centred design phase

**Workshop number**	**Topics covered**	**Objectives**	**Content and tools**	**Duration**
**Introduction**	Presentation of the project		Presentation of the project and participants	**30min**
	Setting the frame		Reminder of confidentiality and the role of each person (facilitators, peer-helper psychologist) Presentation (promotes participation and motivation)	
**Workshop 1**	The case manager Acknowledgements	Questioning the difficulties encountered during the patient care process Define the task profile of the case-manager	Presentation of the patient care pathway using a timeline Definition of the case manager Tools: PowerPoint slideshow drawing on social cognitive theory. The tasks and activities of the case manager and what is not part of his duties: Metaplan activity	**2h30min-3h**
**Workshop 2**	The case manager Resources Acknowledgements	Summary of Workshop 1 Define the general profile of the case manager Identify the necessary resources to be included on the web platform	Creation of a professional identity card listing the skills, knowledge, tasks, profile and training of the case manager Presentation of three ‘persona’ (platform user profiles) representing typic patient or caregiver portraits who could use the platform. Presentation of the platform by the graphic designer: brainstorming on strengths and weaknesses of the proposal identified by the participants (on content and form) Presentation of the web site architecture (different headings and contents) using a summary graph: brainstorming on strengths and weaknesses identified by the participants	**2h30min-3h**
**Workshop 3**	The web platform Acknowledgements	Summary of Workshop 2 Identify the necessary resources to be included on the web platform	Based on the information collected during workshop 2, presentation of version 1 of the platform by the graphic designer Gather feedback from participants. Strengths and limitations of the platform: Metaplan Adaptations envisaged by the participants	**2h30min-3h**
**Workshop 4**	The web platform Conclusion, Closing Acknowledgements	Summary of Workshop 3 Identify the necessary resources to be included on the web platform	Based on the information collected during workshop 3, presentation of version 2 of the platform by the graphic designer Gather feedback from participants. Strengths and limitations of the platform: Metaplan Adaptations envisaged by the participants	**2h30min-3h**

